**Background and rationale**

**a. Gabapentinoids**

Gabapentinoids are a class of medications which was first introduced in the United States (US) and the United Kingdom (UK) in 1993.^1^ The two major agents, gabapentin and pregabalin, were originally developed as antiseizure agents.^2^ They were developed as analogues of gamma-amino-butyric acid (GABA).^3^ However, they do not exhibit any effect on the GABA receptors, nor convert into GABA nor GABA receptor agonists.^4,5^ They also do not appear to control the transport of GABA or its metabolism.^6^

*Mechanism of action and distribution of gabapentinoids*

The mechanism of action of gabapentinoids are not fully understood. Their extensive range of clinical actions is believed to be primarily the result of their inhibitory properties on neuronal voltage-gated calcium channel currents, via impairing the trafficking function of the α2δ subunits, reducing the signal leading to the release of neurotransmitters between synapses in the brain tissue.^7,8^ The α2δ subunits of voltage gated calcium channels are linked to several biological functions, such as enhancing the presence of functional calcium channels on the cell surface, increasing the calcium current within cells, modifying the voltage-dependent activation and inactivation of calcium channels, and accelerating the rates at which these channels activate and deactivate.^4^

Voltage-gated calcium channels are involved in multiple physiological roles in our body. For instance, in the central nervous system, voltage-gated calcium channels also play a role in synaptic transmission.^9^ Activation of voltage-gated calcium channels in cardiac or vascular smooth muscle cells can lead to smooth muscle contraction, which regulates our cardiac rhythm and blood pressure, respectively.^10,11^ In endocrine cells, entry of calcium ions through the voltage-gated calcium channels initiates the secretion of hormones ,such as insulin.^12^ With such wide range physiological functions that voltage-gated calcium channels are involved, despite a lower level found in parts of our body other than the brain, the consumption of gabapentinoids may still have an effect in multiple body systems other than the central nervous system.

With the different pharmacokinetic profiles between gabapentin and pregabalin, the clinical effects exhibited by the two agents may differ from one another and it will be worth investigating how their differences in pharmacokinetic profiles affect their interactions with other conditions or medications.

**b. On and off-label uses of Gabapentinoids**

Licensed indications of gabapentinoids from across the world have since expanded to conditions including neuropathic pain, fibromyalgia, postherpetic neuralgia, restless legs syndrome, generalised anxiety disorder, menopausal symptoms and complications of multiple sclerosis.^13-16^ In addition to their licensed indications, off-label prescribing of gabapentinoids also accounted for a considerable proportion of their use.^17,18^ Given their effects on intracellular calcium levels, a considerable proportion of gabapentinoid prescriptions are for the treatment of mental health symptoms and diagnoses, such as insomnia and bipolar disorder, which, however, have limited evidence of efficacy to support their use.^2,19^

**c. Psychiatric effects of gabapentinoids**

A previous population based cohort study conducted in Sweden suggested that the use of gabapentinoid was associated with an increase hazards of suicidal behaviour and deaths from suicide, unintentional overdoses head/ body injuries and road traffic incidents and offences.^20^ However, such increase is only conclusive for patients at the age of 15-24 years but not for the other age groups.^20^ A recent analysis of studies examining the use of different anticonvulsants, such as pregabalin, has identified a higher likelihood of suicidal thoughts or behaviours when compared to a placebo.^21^ However, The existing studies on this subject have demonstrated a lack of agreement and are hindered by various methodological constraints.^21^

The available evidence on the correlation between gabapentinoids and various psychosocial adverse outcomes is limited. There have been only a few individual case reports describing an increased aggression in children with psychiatric disorders who were taking gabapentin,^22-24^ which are not sufficient to support causality. The lack of evidence in supporting the use of gabapentinoids with other psychiatric medications or in patients with psychiatric co-morbidities should be promptly addressed to ensure patients’ quality of life will not be jeopardised.

**Aims**

To investigate the association between the use of gabapentinoids and risks of psychiatric and somatic outcomes.

**Hypothesis**

The exposure to gabapentinoids will increase the risk of psychiatric and somatic outcomes when compared to unexposed periods.

**Methods**

**Study design**

We will apply the self-controlled case series (SCCS) study design in the proposed study.^25^ The analysis will be conducted on a population of individuals who had experienced both the outcome(s) and exposure of interest, which will be prescription of gabapentinoids. Incidence rate ratios (IRRs) will be calculated by comparing the event rates during periods of gabapentinoid exposure to the rates during all other observed time periods, in other words without gabapentinoid exposure. This will be accomplished using conditional Poisson regression.

This design has a significant advantage over the classical cohort design as included participants will act as their own control and it consequently addresses all potential time-invariant confounding effects that vary between individuals, such as genetic factors and socioeconomic factors.^26^ Additionally, we will account for time-varying factors, such as age and season, which can influence the prescription of gabapentinoids. We will also adjust for the concurrent use of other medications as time-varying factors. Sub-group analysis will also be performed for patients who suffer from mental illnesses, type 2 diabetes or cardiovascular diseases.

This method can investigate associations between acute outcomes and transient exposures^26^ and has been used extensively in literatures studying the safety of psychotropic medications and outcomes such as suicide attempts, self-harm and risk of seizure.^20,27-29^

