**Exposures**

Prescriptions of gabapentin (Anatomical Therapeutic Chemical code N03AX12) or pregabalin (N03AX16) will be identified in CPRD. The exposed period is defined as the time receiving the medication, calculated with the prescription information in CPRD (daily dosages and quantity prescribed).

The index date is defined as the first date of prescription of gabapentinoid medication. We will calculate the length of exposure using information on prescription date and prescribed days in the database. Patients will contribute to consecutive exposure risk periods while they were continuously exposed to the drug.

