**Selection of comparison group**

Included patients will serve as their own control in this study design.^26^ Eligibility will be assessed based on the inclusion and exclusion criteria outlined in the section “Definition of the Study population”. The major advantage of SCCS over the classic design is that it controls for potential effects of measured and unmeasured time-invariant confounders that vary between individuals (i.e. genetic factors, disease severity, and socioeconomic factors).

A 90 days pre-exposure period will be included into the study. Calculation of the IRR during this period of time will be performed to evaluate whether outcomes of interest were caused by the conditions that gabapentinoids prescribed for instead of the use of gabapentinoids, which in turn may introduce bias into the risk estimate during treatment.

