**Statistical Analysis**

Gabapentinoid usage is diverse with multiple indications. It can be prescribed for neuropathic pain, fibromyalgia, postherpetic neuralgia, restless legs syndrome, generalised anxiety disorder, menopausal symptoms, complications of multiple sclerosis, insomnia and bipolar disorder.^2,13-16,19^ There is no other way to estimate their effects for a particular group of patient without using a stratified analysis. SCCS is a method of estimation that focuses on individuals and does not necessitate separate control groups.^33^ As a result, it is considered self-controlled, effectively eliminating the influence of time-invariant factors and we should not include time-invariant factors into the SCCS analysis.

In our study, we will determine the duration of exposure during the study period and compute the incidence rates for the specific outcomes of interest within each exposure risk period. To assess the association between gabapentinoid use and the risk of these outcomes, we will employ conditional Poisson regression. Conditional Poisson regression analysis will enable us to calculate incidence rate ratios (IRRs) by comparing the periods of exposure to gabapentinoids with unexposed periods, adjusted for age in 1-year bands, seasonal effect, and other concurrent medications. Adjusted IRRs, along with their corresponding 95% confidence intervals (CIs), will be estimated for the overall exposure as well as for each predefined exposure risk period. All statistical analyses will be conducted with a significance level of 5%. The calculated IRRs will be stratified by age, sex, ethnicity, types of gabapentinoids, dosage levels and pre-existing comorbidities.

In additional analyses, the interaction between gabapentinoids and opioids or benzodiazepines by comparing the incidence of all-cause drug poisoning across combined exposure windows with periods unexposed to either medication will be examined. Gabapentin-only compared with pregabalin-only treatment periods among individuals who received both drugs during follow-up will also be evaluated.

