A series of sensitivity analyses will be performed, including a spline-based self-controlled case series analysis, exclusion of patients who died within 6 months of the event, starting follow-up from the first neuropathic or chronic pain diagnosis, restricting to individuals with at least two gabapentinoid prescriptions, varying the length of the pre-treatment period, adjusting only for age and season, extending treatment periods. Self-controlled case series extensions analyses will also be conducted.^34^ A negative control analysis will be performed to explore residual confounding. An additional case-case-time-control analysis^35^ is to validate the main findings, in which the 30 days before the event served as the hazard period and were compared with four randomly selected 30-day reference periods 61 to 180 days earlier, future cases occurring 180 to 360 days later were matched by age, sex, and ethnicity, and adjusted odds ratios (aORs) were estimated using conditional logistic regression. A two-sided significance level of 5% was used for all analyses.

For data analysis, we will utilise either the Statistical Analysis System (SAS) or R programming software.

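### Days just after the calculated supply ends sit in the reference period, and the only planned check on them merges them into exposure, so their own poisoning rate is never estimated

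*Protocol*

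**What the plan says.** The Protocol's Study design section contrasts the event rate on gabapentinoids with "the rates during all other observed time periods, in other words without gabapentinoid exposure". The Exposures section fixes where exposure stops: "The exposed period is defined as the time receiving the medication, calculated with the prescription information in CPRD (daily dosages and quantity prescribed". It limits the risk periods to time on drug: "Patients will contribute to consecutive exposure risk periods while they were continuously exposed to the drug". Under Missing data, a median duration is imputed when dosage or quantity is not recorded, so some end dates are estimates.

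One window outside treatment is set apart, under Selection of comparison group: "A 90 days pre-exposure period will be included into the study", with its own IRR. No window after treatment is described. Under Statistical Analysis, adjusted IRRs "will be estimated for the overall exposure as well as for each predefined exposure risk period". The sensitivity analyses in that section include "varying the length of the pre-treatment period, adjusting only for age and season, extending treatment periods". The outcome is all-cause drug poisoning, split into accidental and intentional.

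**The concern.** Taken together, these rules place the days after a calculated supply runs out in the reference. Those days can hold three kinds of time: late refills, continued use of leftover tablets, and the period straight after a real stop. For a drug-poisoning outcome there is no reason to assume in advance that their rate equals that of other unexposed time.

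If it differs, the denominator of the main IRR is contaminated. Lengthening treatment periods does not isolate the problem, because the same days then enter the numerator. Neither analysis reports a rate for them, so a reader could not tell risk on treatment from risk after supply ends, or judge how far the main IRR depends on where the boundary is drawn.

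**Working it through.** The Protocol gives no figure for this point. The only number taken from it is the IRR of 1.5 used under Sample size consideration, here treated as the true on-treatment IRR, R. The rest are assumptions:

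- p: post-supply share of unexposed time
- w: poisoning rate in that time relative to other unexposed time
- e = 0.30: exposed share of observation, so post-supply time is W = 0.70p

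Rates are taken as constant within each type of time, with the same time split for everyone. The pre-exposure window is set aside, and the extension is taken to cover the post-supply days exactly.

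**Main analysis.** The reference rate becomes (1−p)·1 + p·w = 1 + p(w−1), so

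estimated IRR = R / (1 + p(w−1)).

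**Lengthened exposure.** The post-supply days join the exposed days, so

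estimated IRR = (e·R + W·w) / (e + W).

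Results for R = 1.5:

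| p | w | Main | Lengthened exposure |
|---|---|---|---|
| 1% | 2 | 1.5/1.01 = 1.49 | (0.45+0.014)/0.307 = 1.51 |
| 5% | 2 | 1.5/1.05 = 1.43 | (0.45+0.070)/0.335 = 1.55 |
| 10% | 2 | 1.5/1.10 = 1.36 | (0.45+0.140)/0.370 = 1.59 |
| 10% | 1.5 | 1.5/1.05 = 1.43 | (0.45+0.105)/0.370 = 1.50 |
| 10% | 1.2 | 1.5/1.02 = 1.47 | (0.45+0.084)/0.370 = 1.44 |
| 10% | 1 | 1.5/1.00 = 1.50 | (0.45+0.070)/0.370 = 1.41 |
| 10% | 0.7 | 1.5/0.97 = 1.55 | (0.45+0.049)/0.370 = 1.35 |

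With R = 1.0, p = 10% and w = 2, the pair is 1/1.10 = 0.91 and (0.30+0.14)/0.37 = 1.19.

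What follows from the table:

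- The main IRR is right only when w = 1; it is too low when w > 1 and too high when w < 1.
- The lengthened-exposure IRR is right only when w = R.
- For a raised post-supply rate, the two err in opposite directions when w exceeds both 1 and R. When w lies between 1 and R, both fall below the truth.

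**Plausible p.** Observation runs for at most 11 years (2010 to 2020). With 70% unexposed, that is 7.7 years, so a single 30-day stretch is 0.082/7.7, about 1%. Shorter follow-up or repeated courses raise p.

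**With a separate level.** If the window captures the days with the altered rate, the reference rate returns to 1 and the on-treatment IRR returns to R = 1.50 in every row.

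**The case against.** The strongest reply is that the plan already tests this boundary. On days when a patient is still using leftover tablets, counting the time as exposed is correct, and "extending treatment periods" does that; when w = R it recovers the true IRR exactly. Disagreement between the main and lengthened analyses would also show that the boundary matters. This stands, and the extension should be kept. It does not cover a change in rate after a real stop, and agreement between the two is not reassurance: at p = 10% and w = 1.2 they give 1.47 and 1.44, both below 1.5.

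A second reply is that exact windows are often left to a statistical analysis plan, and that the Study design sentence is a summary, since it does not mention the pre-exposure window either. That lowers certainty. But the Protocol does state a rule for the reference and ties its risk periods to time on drug, so an analysis plan that followed it would keep the gap. The other listed checks do not clearly fill it. The spline-based analysis is not described as modelling time since stopping. The case series extensions rest on a cited method paper which, by its title, deals with exposure altered or cut short after the event.

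A third reply is that p, w and e are all assumed. That is correct, and it limits the verdict.

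**Conclusion.** The structural point holds: as written, post-supply days are in the reference in the main analysis and in exposure in the lengthened one, and they are never estimated separately.

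The size is not established. Under w = 2, a true 1.5 becomes 1.49, 1.43 or 1.36 for p of 1%, 5% or 10%; these are illustrations.

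Three stronger readings are tempting, and the Protocol supports none of them:

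- *The main IRR is biased towards the null.* This needs w above 1 and a true IRR above 1, and the Protocol gives no information on w.
- *The two analyses always err in opposite directions, so they bracket the truth.* They do not when w lies between 1 and the true IRR.
- *Neither analysis can give the on-treatment IRR.* The main one does when w = 1, and the lengthened one does when w equals the true IRR.

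Nor does w = 1 clear both analyses: the lengthened one is then diluted (1.41 in the table) unless the true IRR is 1. What the plan lacks is a result from which w could be read.

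**What to change.** Add a post-exposure window of prespecified length after each calculated supply ends, as its own level in the primary conditional Poisson model. Take it out of the reference and report its IRR beside the pre-exposure and on-treatment IRRs. The Protocol gives no basis for a particular length, so the investigators should justify one and vary it in a sensitivity analysis. Do this beside the lengthened treatment periods and not in place of them, because the extension is the right check for continued use of leftover tablets.

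State which window takes precedence when treatment restarts soon enough for the post-exposure window to overlap the next episode's 90-day pre-exposure period. This also requires saying whether that period applies to every episode, which the Protocol does not.

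The text changes are short: a sentence each under Study design and Statistical Analysis, plus the precedence rule. The costs are slightly less reference time and a small loss of precision. The window's IRR will still mix leftover use with true stopping and should be described that way.

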**Setting**

UK primary and secondary care.

**Data source**

Clinical Practice Research Datalink (CPRD) Aurum database, linked to Hospital Episode Statistics (HES) and Office for National Statistics (ONS) Death Registrations.

**Study population**

All Individuals aged 18 or above who received at least one prescription for gabapentinoids (BNF chapter 4.8.1) and received at least one diagnosis of any of the outcomes of interest listed above between 1^st^ January, 2010 and 31^st^ December, 2020 in the CPRD, HES, and ONS Death Registration Data will be eligible for inclusion.

*Observation period*

The observation period will begin on 1^st^ January, 2010 or 18^th^ birthday of the individual or when the patient first join the GP practice (whichever was later) and end on 31^st^ December, 2020 or date of registered death or when the GP practice stops recording healthcare data for that patient (whichever was earlier).

*Exclusion criteria*

Individuals meeting any of the following criteria will be censored:

- Individuals who experienced any of the study outcomes before the observation period will be excluded.
- Patients who have a diagnosis of epilepsy.
- Patients with diagnosed cancer.
- Patients with missing information on date of birth and sex.

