**Outcomes**

All-cause drug poisoning, stratified in accidental poisoning and intentional self-poisoning

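### GP-recorded poisonings dated to the prescribing visit could be counted as exposed on the prescription day, and no planned analysis isolates that day or varies the outcome source

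*Protocol*

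**What the plan says.** The data source is CPRD Aurum, "linked to Hospital Episode Statistics (HES) and Office for National Statistics (ONS) Death Registrations". Under Study population, a patient qualifies with a prescription and an outcome diagnosis "in the CPRD, HES, and ONS Death Registration Data will be eligible for inclusion". The Outcomes section reads, in full, "All-cause drug poisoning, stratified in accidental poisoning and intentional self-poisoning". It does not say which source supplies the event date when the sources differ.

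Exposure comes from one of those same sources: "Prescriptions of gabapentin (Anatomical Therapeutic Chemical code N03AX12) or pregabalin (N03AX16) will be identified in CPRD". Its start is fixed: "The index date is defined as the first date of prescription of gabapentinoid medication". The section then says "Patients will contribute to consecutive exposure risk periods while they were continuously exposed to the drug". Window lengths are not given, and the prescription day is not set apart, so on the natural reading it is ordinary exposed time.

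The check on reverse causation is under Selection of comparison group: "A 90 days pre-exposure period will be included into the study". Statistical Analysis promises an IRR for exposure overall and for each risk period, followed by a long list of sensitivity analyses.

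**The concern.** In a self-controlled case series each patient is their own control, so the information lies in when the event falls relative to exposure. A hospital admission or a death has a date tied to the event. A GP record may instead hold the date of a later consultation. If that consultation is also the one that starts gabapentinoid treatment, a poisoning from days or weeks before is recorded on the first exposed day.

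This error would not average out, because it is tied to the start of exposure. It adds events to the first risk period and takes them from the 90 days before. The early IRR rises, and the pre-exposure IRR, which is meant to warn of trouble, falls.

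Most of the listed sensitivity analyses leave the recorded event dates as they are: a different pre-treatment window, longer treatment periods, a two-prescription minimum, reduced adjustment. A spline could show a spike at treatment start but could not tell late recording from a drug effect. None restricts the outcome source.

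**Working it through.** **The plan's own figure.** Sample size consideration gives n = 484 for IRR 1.5, 5% significance and 80% power, without the exposed share of time r. With p = 1.5r/(1.5r + 1 − r), A = 2[p ln 1.5 − ln(1.5r + 1 − r)] and B = (ln 1.5)² p(1 − p)/A, the signed-root formula is n = (1.96 + 0.842√B)²/A. At r = 0.09: p = 0.129, A = 0.0167, B = 1.11, n = 484. A second solution lies near r = 0.86. So 484 can be reached but not confirmed. It matters here only for the cost of the fix.

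**Assumptions for the bias check** (none is in the documents): true IRR 1.0; flat event rate; one treatment start per case; 3 years observed (1,095 days); first risk window of 30 days; misdated events come from the 30 days before the prescription. From the protocol: the 90-day pre-exposure window, which is separate from reference time, so the reference rate does not change.

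**Formulas.** If a share m of all events is moved to the prescription day, that is 1,095m days' worth of events.

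- Share of the prior 30 days' events needed: q = 1,095m/30
- First-window IRR: 1 + 1,095m/30 = 1 + q
- Pre-exposure IRR: 1 − 1,095m/90
- Overall exposed IRR, exposed share e: 1 + m/e

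| m | q | First 30 days | Pre-exposure | Overall, e = 10% | Overall, e = 30% |
|---|---|---|---|---|---|
| 0 | 0 | 1.00 | 1.00 | 1.00 | 1.00 |
| 0.5% | 18% | 1.18 | 0.94 | 1.05 | 1.02 |
| 1% | 36.5% | 1.365 | 0.88 | 1.10 | 1.03 |

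**Window length.** With a 90-day first window, the same two shifts give 1 + 5.475/90 = 1.06 and 1 + 10.95/90 = 1.12. The bias matters mainly for a short first window.

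**How far it can go.** At 3 years, with 10%, 20% or 30% of time exposed, the 30 days before treatment hold 30/985.5 = 3.0%, 30/876 = 3.4% or 30/766.5 = 3.9% of unexposed events. Moving 3% of unexposed events would need 99%, 88% or 77% of that pool; moving 5% would exceed it every time. Even if the pool were all 90 pre-exposure days, 5% at 10% exposure needs 5/(90/985.5 × 100) = 55% of it. Longer observation tightens the limit: over 6 years (2,191.5 days), moving 1% of all events needs 21.9/30 = 73% of the prior 30 days' events.

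**What would enlarge it.** If the event rate before treatment were k times the reference rate, the first-window IRR would be 1 + kq. With k = 2, q = 18% gives 1.365. Several treatment starts per patient would also enlarge the pool.

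**The case against.** The strongest objection is that the premise is not in the documents. Nothing says that GP records carry entry dates, how many poisonings appear only in GP data, or that such records cluster at prescribing visits. This stands, so the point is conditional. Late recording at a visit with no gabapentinoid prescription would not produce this bias. Where a hospital admission is also on file, a later GP record does harm only if it replaces the admission date or is counted again.

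Second, date rules and the merging of duplicate records commonly sit in a statistical analysis plan, which is not shown. Taken alone, those would not be a finding. But the protocol itself fixes the three sources, the exposure start and a detailed sensitivity list, and that list does not test this threat.

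Third, the case-case-time-control analysis uses the 30 days before the event as its hazard period. Read literally, a first prescription on the recorded event day falls outside it, so that analysis is partly protected. The negative control analysis addresses residual confounding. Neither isolates the prescription day in the main analysis, and a disagreement between designs would not identify the cause.

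A reader might infer three stronger things. One is that the protocol accepts the sources on equal terms; it is only silent on ranking. Another is that poisonings are in fact misdated and the IRR inflated; the documents show only that this could happen. The third is that the bias could by itself produce the planned overall IRR of 1.5. The arithmetic for that is (0.1 + 0.9 × 0.05)/0.1/0.95 = 1.53, but it needs 5% of unexposed events moved at 10% exposure, more than the preceding 30 days contain under the assumptions above.

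**Conclusion.** The concern holds as a design weakness, not as a demonstrated bias. The outcome sources and the start of exposure let a GP-recorded poisoning share a date with the first prescription, and no listed analysis restricts the outcome source or directly isolates that day. If some of those dates belong to the visit rather than the event, the direction is clear: first-period IRR up, pre-exposure IRR down. A defensible size is an early IRR of about 1.18 to 1.36 under no true effect, against an overall IRR of about 1.02 to 1.10. Both rest on an assumed 0.5% to 1% of events moved, a 30-day window, 3 years of observation, one start and flat risk. With no misdating there is no bias. The early estimate is the one at risk, and the protocol commits to reporting it. The change is worth making.

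**What to change.** 1. Under Exposures, put the prescription day in its own one-day window, outside both the exposed and the reference periods, and report its event count and IRR separately.
2. Under Outcomes, date an episode by the HES admission date or the ONS date of death where one exists, and treat GP records close to it, within a stated interval, as the same episode.
3. Under Statistical Analysis, add a sensitivity analysis restricted to HES- or ONS-recorded poisonings.

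Making hospital and death records the sole primary outcome is a debatable trade-off and is not needed to meet the point.

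The cost is a little extra analysis and slightly fewer events in the first risk window. The restricted run loses GP-only poisonings, whose share is unknown, so its precision will be lower, most of all in the strata. The figure of 484 gives no reassurance there: it covers one overall comparison at IRR 1.5, not the accidental and intentional split, the separate risk periods or the subgroups.

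### Observation opens at practice joining with no run-in, so people who join already on treatment are dated as new starters and the 90-day pre-exposure check is slightly distorted and truncated

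*Protocol*

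**What the plan says.** Protocol, Study population (Observation period): observation starts at the latest of three dates, the third being "when the patient first join the GP practice (whichever was later". No minimum prior registration is attached. The exclusion criteria in the same section add: "Individuals who experienced any of the study outcomes before the observation period will be excluded".

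Protocol, Exposures: gabapentin and pregabalin prescriptions "will be identified in CPRD", and "The index date is defined as the first date of prescription of gabapentinoid medication". No washout or new-user condition is set.

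Protocol, Selection of comparison group: "A 90 days pre-exposure period will be included into the study". Its IRR is to be used "to evaluate whether outcomes of interest were caused by the conditions that gabapentinoids prescribed for instead of the use of gabapentinoids".

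Outcomes have wider sources than prescriptions. CPRD Aurum is "linked to Hospital Episode Statistics (HES) and Office for National Statistics (ONS) Death Registrations" (Data source), and eligibility rests on diagnoses "in the CPRD, HES, and ONS Death Registration Data will be eligible for inclusion" (Study population).

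**The concern.** The index date, the pre-exposure window and the prior-outcome exclusion all look back in time. For anyone whose observation starts at joining, the start rule provides no earlier registered time in which to look.

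Take a treated person who moves practice. The first prescription at the new practice becomes the index date. The days from joining to that prescription are classed as pre-exposure or unexposed although the person may be on drug. The window ends at the joining date, so it holds fewer than 90 days. HES cannot supply the missing prescriptions, because exposure is taken from CPRD alone.

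The pre-exposure IRR is the plan's stated check on whether events reflect the underlying condition. Any registration artefact falls inside that window.

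**Working it through.** **The plan's own figures.** The protocol gives no figure for the share of joiners, the share already treated, or the delay to the first prescription. There is nothing to reproduce, so these enter as assumptions with a range.

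**Inputs.**
- Window length: 90 days (Selection of comparison group).
- True on-treatment IRR: 1.5 (Sample size consideration).
- f, the share of cases who are continuing users joining a practice: 5-20% (assumed).
- g, days from joining to the first recorded prescription: 7-30 (assumed).
- True pre-exposure IRR: 1.0, and 2.0 for contrast (assumed).

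**Pre-exposure IRR.** Other cases contribute a full 90-day window. Continuing joiners contribute g days, all on drug. The share of recorded pre-exposure time that is really exposed is

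m = f·g / [(1 − f)·90 + f·g].

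Treating rates as pooled across cases, which approximates the conditional model, the observed pre-exposure IRR = (1 − m)·(true pre-exposure IRR) + m·1.5. The share of window time lost to truncation = f·(90 − g)/90.

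Example, f = 20% and g = 30: m = 6/(72 + 6) = 0.077. The observed IRR is 1 + 0.077 × 0.5 = 1.038, and the time lost is 0.20 × 60/90 = 13.3%.

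| f | g | m | Observed, truth 1.0 | Observed, truth 2.0 | Window time lost |
|---|---|---|---|---|---|
| 5% | 7 | 0.004 | 1.002 | 1.998 | 4.6% |
| 5% | 30 | 0.017 | 1.009 | 1.991 | 3.3% |
| 10% | 14 | 0.017 | 1.008 | 1.992 | 8.4% |
| 20% | 7 | 0.019 | 1.010 | 1.990 | 18.4% |
| 20% | 30 | 0.077 | 1.038 | 1.962 | 13.3% |

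The pre-exposure IRR is pulled toward the on-treatment IRR: up from 1.0, down from 2.0. If the drug has no effect and there is no pre-exposure effect, all rates are equal and misclassified days cause no shift.

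**Main IRR.** If a share q of reference time is really exposed, the observed IRR = 1.5/(1 + 0.5q).
- q = 1%: 1.5/1.005 = 1.493.
- q = 5%: 1.5/1.025 = 1.463.

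This range of q is generous. At f = 20% and g = 30 the average is 6 misclassified days per case. That is 1% of reference time only if a case has 600 reference days, and 5% only if it has 120. Gaps under 90 days also fall inside the pre-exposure window, so they reach the reference only if that window is not modelled separately.

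**Simulation check.** In 400,000 simulated cases over 11 years, 40% joined mid-study and half of those were continuing users, which gives f = 20%. With a true IRR of 1.5, the exposed IRR came out at 1.45-1.49. A separate simulation of 300,000 cases with the same shares gave 1.49-1.52 for the exposed IRR. With no historic events added, its pre-exposure IRR was 0.99-1.02. Both agree that the effect is small.

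**Do the listed sensitivity analyses (Statistical Analysis) cover it?** Changing the pre-treatment window length keeps the same start date. Moving follow-up to an initial pain diagnosis requires no prior registration. Requiring two or more prescriptions does not separate new from continuing users. None adds a registration look-back.

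**The case against.** The strongest objection is that SCCS does not need new users. Exposure is built from each prescription's dates and duration, so a continuing user's later exposed time is classed correctly and the main IRR barely moves. This stands. The harm is confined to the gap after joining, the shortened window and analyses by time since start.

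It also stands that only people whose latest start date is joining are affected. Those registered before 2010 have earlier CPRD history.

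Look-back length and the data source for an exclusion are often left to a statistical analysis plan, so their absence is not counted as a fault. The start date is different: the protocol fixes it in full.

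A reader might infer two stronger claims.
- *The prior-outcome exclusion fails altogether for joiners.* The documents do not support this. Linked HES is hospital data and is not tied to the date of joining a practice, so earlier hospital-recorded poisonings can be found. Only outcomes recorded solely in primary care are at risk.
- *The pre-exposure check is badly biased.* If 3-10% of joiners' events are old poisonings dated near registration, and 30-50% of cases are joiners, simulation gives a null pre-exposure IRR of 1.07-1.39. That result comes from the assumed back-dating. Nothing in the protocol shows that historic poisonings are entered with a registration date. Some would also appear in HES with their true date and trigger the exclusion.

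**Conclusion.** The point holds as a modest weakness in a fixed rule. As written, people who join a practice while on treatment are dated as starters, some on-drug days count as pre-exposure or unexposed, and their 90-day window is truncated. The prior-outcome exclusion is weaker, but not void, for joiners.

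Over the assumed range (f 5-20%, g 7-30 days, true IRR 1.5, true pre-exposure IRR 1.0), the pre-exposure IRR shifts by about 0.002-0.04. Roughly 3-18% of window time is lost. A main IRR of 1.5 reads about 1.45-1.49. These sizes rest on shares that the documents do not give. The conclusions about gabapentinoids would be unlikely to change. The case for acting is that the remedy is cheap and protects a check the plan relies on.

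**What to change.** In Study population (Observation period), start observation at the latest of 1 January 2010, the 18th birthday, and practice registration plus a run-in at least as long as the 90-day pre-exposure window. Run a 12-month run-in as a sensitivity analysis.

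Use the run-in together with all earlier CPRD and HES records to apply the prior-outcome exclusion and to flag continuing users. As a further sensitivity analysis, estimate both the pre-exposure and the exposed IRR in people with no gabapentinoid prescription in the run-in. Both must come from the same people, because the plan reads one against the other.

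The cost is a sentence in the protocol, a date shift in the extraction, and some cases: about 6-8% with 90 days and 18-20% with 12 months if 40% of cases are joiners (assumed). For scale, the protocol requires 484 cases and claims adequacy down to 0.1% incidence. In its roughly 1,197,000 users that is 1,197 cases, and a 20% loss leaves about 958. That user count adds the two drugs' totals, so it may count people twice, and it precedes the exclusions. The margin will be thinner in the planned strata and in the gabapentin-only versus pregabalin-only comparison, which is one reason to keep 12 months as a sensitivity analysis.
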